### Intervention: oral rehabilitation

Individual treatment options will be discussed with the patients and rehabilitation will be provided depending on the clinical situation and the patient’s financial status. The rehabilitation will include fixed prosthodontics and will be achieved by providing the latest and most effective measures in modern-day prosthodontics. Briefly, the procedures will involve a control phase involving scaling, root planning, oral hygiene instructions, etc. When needed, extractions and bone augmentation will be performed, and also temporary removable dentures will be made if required. This will be followed by the restoration of the vertical dimension with occlusal splints (if needed), tooth preparations, placement of dental implants (if needed), and finally cementation of dental crowns. The entire rehabilitation phase is estimated to take approximately 3–12 months, where implant treatment is the main factor for the longer time frames.

### Outcome parameters and measurements

Test measures are NA with good psychometric properties, i.e., good reliability (with minimum measurement errors), validity (measures the construct intended), and responsiveness (sensitivity to detect changes over time). The primary outcome is the changes in episodic memory and learning measured by the Brief Visuospatial Memory Test-Revised (BVMT-R) [43]. All secondary outcomes have been listed and summarized below in Tabel 2, two of them are corresponding changes in neuro correlates at MRI and the masticatory performance assessed by the mixing degree of the two colored gum.

*Masticatory function* The chewing function will be assessed both objectively and subjectively. The masticatory function will be evaluated using a well-established two-color chewing gum mixing test (Orophys smart chew GmbH, Bern, Switzerland) during a standardized and deliberate chewing sequence of 20 cycles in accordance with the recommended instructions [44, 45]. Accordingly, the participants will be asked to chew on the two-colored chewing gum on their preferred chewing side. The participants will be abruptly stopped by the examiner and asked to spit out the chewing gum after twenty chewing cycles. The examiner will silently count the number of chewing strokes during the tests. The chewed samples will be photographed with a phone camera (iPhone, Apple Inc.) on a specially designed stand before flattening the sample into a wafer of 1 mm thickness. The images will be imported into a photo‐editing software (Adobe Photoshop® Elements for Windows, Adobe systems incorporated, San Jose, CA, USA), both sides of the wafers will be assembled into a single image file. These files are then to be imported and analyzed in a purpose‐built freeware (ViewGum©, dHAL Software, Greece, www.dhal.com) which calculates the Variance of Hue (VoH), a parameter on the color mixing of the chewing gum.

The oral health-related QoL assessed by the participants will be evaluated with the OHIP-14 questionnaire and subject-based information on chewing ability will also be collected. These measurements will be used to assess the degree of functional impairment (pretest) and the subsequent effect of restoration of function (post-test) on masticatory function.

*Neuropsychological assessments* The NA are approximated to 90 min per test occasion and are conducted prior to the protocol by a research assistant blinded to the randomization. The neuropsychological assessments are state-of-the-art tests with good psychometric validity translated into Swedish. The aim is to use the cognitive tests that are sensitive to change and measure a broad range of cognitive domains.

The assessed cognitive domains and specific tests are:

*Episodic memory* The Ray Auditory Verbal Learning Test (RAVLT) [46], the BVMT-R [43].

*Executive functions* The Trail Making Test (TMT) trial 4 from Delis-Kaplan Executive Function System (D-KEFS) [47], the Verbal Fluency (VF) test from D-KEFS, and the Color-Word Interference Test from D-KEFS.

*Attention/working-memory* The Digit Span from Wechsler Adult Intelligence Scale (WAIS) 4th edition[48], the Digit Symbol from WAIS-IV, and the Trail Making Test (TMT) trial 1–3, and 5 from D-KEFS.

*Visuospatial functions* The Block Design from WAIS-IV.

*Logical thinking* The Matrix Reasoning from WAIS-IV.

*Brain imaging* All the Magnetic Resonance Imaging (MRI) acquisitions will be conducted at SUBIC using a Siemens Prisma 3 T scanner (Erlangen, Germany). The duration of the MRI protocol is approximately 40 min and it includes a high resolution sagittal T1-weighted MPRAGE sequence for structural changes, a T2-FLAIR sequence to exclude other types of pathologies such as tumors, and detection of white matter pathology. Further, for the resting-state functional MRI (i.e., the participants don’t perform any cognitive task but are instructed to stay awake during the scanning), an EPI blood oxygen level-dependent (BOLD) sequence will be used. A Pseudo-Continuous Arterial Spin Labeling (pCASL) sequence will be performed to measure brain perfusion. Finally, we also aim to include measures of the masseter muscle in the MRI to be able to study pre- and post-muscle volume using a PD-weighted SPACE sequence. The MRI data will be stored and analyzed within TheHiveDB which is an encrypted web-based neuroimaging database system capable of managing data for large longitudinal projects [49]. The system has the capacity to perform fully automated analysis of structural and functional imaging data using a variety of algorithms from Freesurfer, SPM, and FSL, etc. A detailed quality control protocol will be used to ensure the image quality [50] and a radiologist at Karolinska University Hospital, Stockholm, Sweden, will assess the images.

*Saliva samples* Subjective stress of the participants before the saliva collection will be assessed with a Hospital anxiety depression scale questionnaire. Saliva will be collected to measure cortisol levels as a measure of stress. Stimulated saliva will be collected by having the participant chew on paraffin gum and spit out the saliva in a cup for 2 min. The amount of stimulated saliva will be noted and then approximately 5 ml will be collected in a tube and frozen at -80 degrees C for later analyzes. The time of conducting the test will be matched for all tests to avoid bias with fluctuating levels throughout the day. Participants will be instructed not to eat or drink for about two hours before the test.

*Ethical issues* The regional ethical review board in Stockholm has approved the study (Dnr: 2012/652-31/1). An amendment (Dnr 2016/670-31/2) on the updated protocol has been accepted by the ethical review board, Stockholm. All participants will be given oral and written information about the study, and a signed written informed consent will be obtained prior to randomization and initiation of any testing. The data generated from the study will be stored following the Swedish Archives Act and the Personal Data Act.

### Statistical methods

The data from the study will be entered in a Microsoft Excel sheet and exported to statistical software packages like SPSS Inc, Statistica, StatSoft Inc, or similar advanced analytics software packages for analysis. The result from the cognitive testing will be analyzed as repeated measure Analysis of covariance (ANCOVAs) with groups (experimental and control) and time (pre-and post-rehabilitation) as factors. Group-by-time interaction, the main effect of the group, and the main effect of time will be evaluated. To compare the magnitude of gains, the effect size (partial eta-square) will also be calculated. We will use time-length between pre-and post-tests as a covariate of interest with aiming to better control group differences. To predict the intervention outcomes, we will develop models that mainly predict cognitive test measures (NA). Predictive ability is defined as the amount of variance in the outcome that can be explained by pre-test cognitive status (slope method). Explained variance in the outcome will be obtained by analyzing linear regressions.

Preprocessing and statistical analyses of MRI data will be performed with Statistical Parametric Mapping (SPM) run in MATLAB (MathWorks). Movement correction will be performed by realigning and unwarp to the first image in the series. To consider group-specific anatomical brain differences, all patients will be normalized to Montreal Neurological Institute (MNI) echoplanar-imaging template. However, cortical thickness measures will not be normalized but rather used in their raw form. For cortical segmentation, a Freesurfer pipeline will be applied to the MRI images to produce regional cortical thickness and volumetric measures. To investigate rehabilitating-related changes repeated measures ANCOVAs will be performed with the groups (experimental and control) and time (pre-and post-rehabilitation) as factors. We will control for multiple comparisons with the Bonferroni-Holm method since all cognitive tests are correlated and because a majority of the test variables in this study belong to the same family (cognitive domain) or even the same test. In case of significant behavioral effects (i.e., a significant group-by-time interaction effect indicating that: the experimental group improves their cognitive performances > the control group), the changes will be evaluated as covariates of interest in relation to the potential brain changes.

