The study follows a clinical, longitudinal randomized trial design and has considered any possible bias due to type 1 error. Accordingly, the two pre-tests in the control group are included to rule out for test–retest effects of the cognitive measurements. The likelihood of the participants performing better in the cognitive tests in the second assessment is quite high. Therefore, the post-test in the control group will rule out any type 1 error due to an improvement over time that could potentially be interpreted as an improvement due to the intervention (dental rehabilitation). We hypothesize that at post-test (after the intervention), the experimental group will perform better in cognitive tests than the control group at post-test (i.e., the intervention improves the cognitive abilities better than what the test–retest effect does). However, at post-test 2 (after the intervention), we hypothesize that the control group will perform at a similar level as the experimental group as a result of gained effects due to the intervention. Importantly, the control group will probably have a shorter time length between pre-and post-test than the experimental group. This is a limitation that might lead to a greater risk of type- 2 errors and thereby decrease the possibilities to detect intervention effects. However, due to ethical reasons, we cannot deny the control group their dental rehabilitation any longer than 3–4 months after the pre-tests (see the method section for further information on the control for time differences between pre-and post-test). In contrast, if we detect positive intervention effects, we will be able to draw firm conclusions (i.e., despite a shorter time between pre-and post-test for the control group). Importantly, we will also evaluate if we can identify pre-intervention predictors for intervention outcomes. This is especially important regarding cognitive status (assessed with the pre-intervention neuropsychological tests) and we will therefore statistically model cognitive performances to predict intervention outcomes.

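### The primary BVMT-R analysis is a change-score test that does not adjust for the pre-test score; adding it would gain precision at almost no cost

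*Protocol article*

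**What the plan says.** The protocol article, under Outcome parameters and measurements, defines the endpoint as a change: "The primary outcome is the changes in episodic memory and learning measured by the Brief Visuospatial Memory Test-Revised (BVMT-R").

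Under Statistical methods the model is a "repeated measure Analysis of covariance (ANCOVAs) with groups (experimental and control) and time (pre-and post-rehabilitation) as factors". One covariate is named: "We will use time-length between pre-and post-tests as a covariate of interest with aiming to better control group differences". Three effects are then listed: "Group-by-time interaction, the main effect of the group, and the main effect of time will be evaluated". Later in the section, the result that counts as a behavioural effect is described as "a significant group-by-time interaction effect indicating that: the experimental group improves their cognitive performances > the control group".

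The pre-test score enters as a regressor only in separate prediction models: "Predictive ability is defined as the amount of variance in the outcome that can be explained by pre-test cognitive status (slope method").

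The Discussion expects a practice effect: "The likelihood of the participants performing better in the cognitive tests in the second assessment is quite high". It uses the control group's untreated post-test to separate that effect from benefit. Its hypothesis is that the experimental group will do better than controls at post-test.

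**The concern.** The model is called an analysis of covariance, but the covariate is the interval, not the baseline score. The pre-test sits on the outcome side, as one of the two levels of time. The interaction is then a difference in mean change, which carries the noise of the pre-test in full. Adjusting the post-test for the pre-test removes only the part of the pre-test that predicts the post-test, and usually gives a narrower interval for the same treatment effect.

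What is at stake is precision in a trial that expects about 30 evaluable patients per arm. A second, smaller matter is that three effects are listed together and none is formally named as the confirmatory contrast.

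This is not a detail left to an analysis plan that is not shown. The article itself fixes the factors and names the covariate.

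**Working it through.** **Inputs from the article (Sample size).** Partial eta-squared 0.06, alpha 0.05, power 0.80, 30 per group, dropout 20–25%, 40 per group enrolled. **Not in the article:** the pre-post correlation of BVMT-R (rho) and the ratio of pre to post standard deviations. I assume rho from 0.3 to 0.9 and equal variances.

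**1. The plan's own figure.** The dropout step reproduces: 30/(1 − 0.25) = 40. The 30 per group does not follow from the stated inputs alone. With f² = 0.06/0.94 = 0.0638 placed directly on the interaction, the noncentrality at 60 patients is 0.0638 × 60 = 3.83 and power is 48.6%; 80% power needs 126–128 in total. A within-between repeated-measures formula with two occasions needs 64 in total at rho = 0 and 34 at rho = 0.5. The figure therefore depends on an unstated correlation and effect-size convention. This point does not rest on it.

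**2. What the interaction tests.** With two occasions, the group-by-time F test is the test of arm in a regression of (post − pre) on arm, plus the interval where that covariate is included.

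**3. Relative precision.** In units of the common variance, the variance of the arm difference is proportional to:
- change score: 2(1 − rho)
- baseline-adjusted: 1 − rho²

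The ratio is 2/(1 + rho), so the gain in effective sample size is 2/(1 + rho) − 1. The last column takes eta-squared 0.06 as applying directly to the interaction; the unadjusted value is then 48.6%.

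| rho (assumed) | change | adjusted | gain | 60 patients act like | power after adjustment |
|---|---|---|---|---|---|
| 0.3 | 1.40 | 0.91 | 53.8% | 92.3 | 66.5% |
| 0.5 | 1.00 | 0.75 | 33.3% | 80.0 | 60.3% |
| 0.7 | 0.60 | 0.51 | 17.6% | 70.6 | 55.0% |
| 0.8 | 0.40 | 0.36 | 11.1% | 66.7 | 52.7% |
| 0.9 | 0.20 | 0.19 | 5.3% | 63.2 | 50.6% |

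The power column leaves out the interval covariate, so it shows the direction and rough size of the gain. It is not the power of the planned model.

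**4. Finite-sample check.** In 20,000 simulated trials with 30 per arm, the variance ratio (change over adjusted) was 1.29 at rho 0.5 and 1.09 at rho 0.8, against 1.33 and 1.11 in theory. Both estimators recovered the true effect of 0.50 SD.

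**5. Unequal variances.** In general the variance saved is proportional to (SDpre − rho × SDpost)². It is never negative, but it vanishes when SDpre/SDpost = rho, for example 0.8 at rho 0.8.

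**6. Chance imbalance.** At 30 per arm the baseline difference has a standard error of √(2/30) = 0.26 SD. Given an imbalance D, the change-score contrast is off by (1 − rho)D. One standard error gives 0.5 × 0.26 = 0.13 SD at rho 0.5, or 0.3 × 0.26 = 0.08 SD at rho 0.7. Baseline adjustment removes this.

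**7. Main effects.** The group main effect averages the pre-test, where no effect can exist, with the post-test. In the simulation a true 0.50 SD came out as 0.25 SD. The time main effect pools both arms and includes practice. Neither tests efficacy.

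**8. The interval covariate.** Controls are retested after about 3 months (3–4 in the Discussion). The experimental group is retested at least 3 months after a rehabilitation phase of roughly 3–12 months, so at about 3 + 3 = 6 months or later. On these figures the two arms' intervals hardly overlap.

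**The case against.** The strongest reply is that nothing here is an error. A change-score comparison in a randomised trial is unbiased and matches an endpoint defined as change. Preferring baseline adjustment is a choice between two valid analyses. That stands: the loss is of efficiency, not validity.

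It is also fair that the size of the gain is unknown. A reader might take 11–33% as a property of this trial. It is only what follows from assumed correlations of 0.5–0.8 with equal variances. At rho 0.9 the gain is about 5%, and with unequal variances it can vanish.

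A reader might infer from the list of three effects that a significant main effect could be claimed as benefit, and might put the chance of a false positive on either group or interaction at 1 − 0.95² = 9.75%. The article does not support that. It reads the group-by-time interaction as the sign of benefit, never says that a main effect shows efficacy, and explicitly uses the control group's untreated post-test to guard against mistaking practice for benefit. What remains is a request to name one contrast formally.

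Finally, replacing the model with arm and pre-test alone would silently remove the interval covariate, which the article presents as its control for unequal follow-up. That objection is right, and the change below takes account of it.

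**Conclusion.** The point holds as a matter of efficiency. The planned interaction is an interval-adjusted change-score test without baseline adjustment. Adding the pre-test BVMT-R would be worth about 33%, 18% or 11% more patients at rho 0.5, 0.7 or 0.8, and 54% to 5% over rho 0.3–0.9, slightly less at 30 per arm. These figures assume equal pre and post variances and a correlation that the article does not give. Apart from the small finite-sample loss, the direction does not depend on rho; the size does.

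A reader might go further and conclude that the analysis is biased, or that the trial is shown to be underpowered. Neither follows. Randomisation makes the change-score test unbiased, and the failure to reproduce 30 per group reflects unstated inputs and does not prove the figure wrong.

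**What to change.** Make the primary analysis a regression of post-test BVMT-R on arm and pre-test BVMT-R, or the equivalent mixed model with the baseline mean constrained equal across arms.

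Define the post-test for each arm: for the experimental group, the first post-test after rehabilitation; for the control group, the untreated post-test at about 3 months, before rehabilitation. Controls also have tests after rehabilitation, so a label such as first follow-up would be ambiguous.

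Name the arm coefficient as the single confirmatory contrast, reported in BVMT-R points with a 95% confidence interval. Treat the group and time main effects as descriptive.

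State explicitly whether the interval covariate stays in the primary model, moves to a sensitivity analysis or is dropped, and why. Because it is closely tied to arm, this choice affects both the meaning and the precision of the arm coefficient.

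Cost: a change of wording and one degree of freedom. The pre-test score is already collected, so no new data, visits or patients are needed.

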### Study participants

The study will include patients seeking fixed prosthodontic treatment either due to reduced dentition measured by Eichner’s index [36] and complaining of impaired chewing ability due to a reduced number of posterior functional units or reduced dentition in general. Efforts will be made to recruit an equal number of men and women. The criteria for inclusion (Table 1) are patients in the age range of 65–80 years, in need of prosthodontic treatment, and presenting a Mini-Mental State Examination (MMSE) score > 25 [37]. The MMSE is a screening tool that has shown to be a sensitive marker of overt dementia and will therefore help us to discriminate between normal cognitive status and individuals at risk of dementia. However, MMSE is not a cognitive test that is suitable for intervention evaluation because many patients will perform at a maximum or near-maximum level (i.e., ceiling effect), leaving no opportunity to detect improvement across time [38]. On the contrary, our outcome tests with the neuropsychological assessments (NA) are highly sensitive to change (see heading outcome parameters and measurements). Thus, we aim to exclude patients with overt dementias (with low potential of cognitive improvement after intervention), but we remain open to including patients within the cognitive continuum from normal performances to mild cognitive impairments (with higher potential of cognitive improvement by the intervention). Circumstances that could compromise the validity of the tests, such as poor Swedish language skills, reading disabilities, severely reduced hearing or vision, are also considered as a criterion for exclusion, depending on the severity of the condition. Patients without any subjective masticatory dysfunction and patients that will be rehabilitated with removable dentures are excluded. Specific criteria are used to determine eligibility for the (optional) MRI acquisitions (Table 1). The demographic details (height, weight, etc.,) along with self-reports of ongoing medications (if any) and chewing ability are collected. The participants are screened with Alcohol Use Disorders Identification Test (AUDIT) [39, 40] and the oral health-related QoL of the participants is assessed with Oral Health Impact Profile (OHIP-14) [41]. The hospital anxiety and depression (HAD) scale will be used to measure the anxiety and depression in the groups [42]. The number of remaining teeth and occluding units are collected from the dental record (intraoral photos and dental X-rays).

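### Variance explained by the pre-test score is a prognostic measure and cannot show who responds to rehabilitation

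*Protocol article*

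**What the plan says.** The Statistical methods section of the protocol article describes two separate analyses of the cognitive data. The first is a repeated-measures ANCOVA with group and time as factors, which addresses mean effects. The second is a prediction analysis:

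- Its aim: "To predict the intervention outcomes, we will develop models that mainly predict cognitive test measures (NA".
- Its measure: "Predictive ability is defined as the amount of variance in the outcome that can be explained by pre-test cognitive status (slope method".
- Its estimation: "Explained variance in the outcome will be obtained by analyzing linear regressions".

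The Discussion gives the purpose: "we will also evaluate if we can identify pre-intervention predictors for intervention outcomes". It describes this as especially important for cognitive status.

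The prediction analysis has no arm term, no arm-by-pre-test interaction and no comparison with untreated patients. The slope method is not explained. The text does not say whether the outcome in these regressions is the post-test score or the change, although the section on outcome parameters defines the primary outcome as change.

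**The concern.** A pre-test score is related to a later score on the same test, and to the change between the two, whether or not anything was done in between. A regression on the pre-test without an untreated comparison therefore returns a non-zero R-squared even for a treatment with no effect. If that figure is read as evidence about who responds to rehabilitation, retest behaviour is mistaken for response.

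The plan sees the same problem for means. The Discussion says of retesting: "The likelihood of the participants performing better in the cognitive tests in the second assessment is quite high", and it uses the control group's untreated retest to deal with that. The prediction analysis, as defined, does not use that control.

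At stake is a secondary conclusion of the trial, namely which patients are reported as predicted to do well because of rehabilitation.

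**Working it through.** **Inputs.** The plan gives no figure for this analysis, so there is none to reproduce. The Sample size section needs 30 per group and enrols 40, which agrees with its upper dropout rate: 30/(1 − 0.25) = 40. The section on outcome parameters claims "good reliability (with minimum measurement errors" for the tests but states no coefficient. I therefore assume a test-retest correlation ρ of 0.5 to 0.9 and equal SDs (σ) at both tests. The treatment effect is set to zero.

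**Outcome = change.** With pre-test X and post-test Y:

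- Cov(Y − X, X) = ρσ² − σ² = −(1 − ρ)σ²
- Var(Y − X) = 2(1 − ρ)σ²
- Slope = −(1 − ρ)
- R² = (1 − ρ)²/[2(1 − ρ)] = (1 − ρ)/2

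This is regression to the mean: the pre-test stands on both sides of the equation.

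**Outcome = post-test score.** Slope = ρ and R² = ρ². This is test stability.

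Adding the same constant to every post-test score, whether a practice gain or a uniform treatment effect, changes none of these values. R² is thus the same for no benefit and for equal benefit to all.

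**Numbers.** The last two columns come from simulating 20,000 trials per cell with zero effect. They give the share of trials in which an ordinary two-sided 5% test calls the pre-test a predictor.

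| ρ (assumed) | R², change | Slope, change | R², post-test | Flagged, change (n = 30 / 40 / 60) | Flagged, post-test (n = 30) |
|---|---|---|---|---|---|
| 0.5 | 0.25 | −0.5 | 0.25 | 83% / 93% / 99% | 83% |
| 0.6 | 0.20 | −0.4 | 0.36 | 73% / 84% / 96% | 95% |
| 0.7 | 0.15 | −0.3 | 0.49 | 58% / 71% / 88% | 99.6% |
| 0.8 | 0.10 | −0.2 | 0.64 | 41% / 52% / 71% | 100% |
| 0.9 | 0.05 | −0.1 | 0.81 | 23% / 29% / 41% | 100% |

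A valid test of differential response would flag 5%. Simulated mean R² exceeded the formula by at most 0.03, the usual small-sample excess. The plan names no significance test here, so the last two columns are illustrative; the R² values follow from its definition.

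**Single example.** At ρ = 0.7, the correlation of change with pre-test is −√0.15 = −0.387. With n = 60, t = −0.387 × √(58/0.85) = −3.2, p about 0.002, with no treatment effect.

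**Alternative.** In a model with arm, pre-test and arm × pre-test, the interaction was falsely significant in 4.3% to 5.3% of 4,000 simulated null trials per cell (ρ = 0.5, 0.7, 0.9; 30 or 40 per arm; same ρ in both arms). At ρ = 0.7, its power is:

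| Slope difference (SD per SD of pre-test) | 30 per arm | 40 per arm |
|---|---|---|
| 0.5 | 72% | 84% |
| 0.25 | 26% | 32% |

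**The case against.** **The analysis may be meant as prognosis.** The article speaks of outcomes, not of differential benefit, and R-squared is a proper measure for prognosis. This stands as a limit: the point applies only to claims about response to rehabilitation. The Discussion leans towards such claims without making them explicitly.

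**An article may leave the model terms to a fuller document.** That is fair for the undefined slope method. It does not cover the measure itself, which is published as a definition and has no untreated comparison in it.

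**A stronger reading is tempting but not supported.** A reader might infer that the plan expects lower scorers to gain more, that the method would confirm this by construction, and that care could then be steered towards low scorers. The phrase behind this, "with higher potential of cognitive improvement by the intervention", stands in the Study participants section as an eligibility rationale. It sets the included range, from normal performance to mild impairment, against excluded overt dementia, for which little improvement is expected. It is at best ambiguous and does not clearly predict larger gains at lower scores. The appearance that low scorers gain arises only if the outcome is change, which the Statistical methods section does not specify; with the post-test score the slope is positive. Nothing in the document speaks of steering care.

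**Good reliability shrinks the artefact.** This is true for change, where R² falls to 0.05 at ρ = 0.9. For the post-test score the opposite holds, and R² rises to 0.81.

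**The interaction is not clean in this design either.** This stands. Under Study design the controls are retested after about 3 months. The experimental group is tested at least 3 months after a rehabilitation estimated at 3 to 12 months, so about 6 to 15 months or more from pre-test. If ρ were 0.8 in controls and 0.7 in the experimental group (assumed), a null treatment would give a slope difference of 0.7 − 0.8 = −0.1. The false-positive rates above assume a common ρ and do not cover this.

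**Conclusion.** The point holds as a limit on interpretation. As defined, predictive ability cannot separate response to rehabilitation from retest behaviour, whichever outcome is meant. The lack of separation does not depend on the value of ρ; only the size of the null R-squared does, and the 0.5 to 0.9 range and equal SDs are assumptions. As plain prognosis the measure is legitimate. The analysis is a supporting one, is not among the outcomes in Table 2, and leaves the primary group-by-time comparison untouched. It is worth correcting before analysis but does not threaten the trial's main result.

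**What to change.** - For any claim about response to rehabilitation, take the experimental group's first post-rehabilitation score and the control group's untreated second score (before its own rehabilitation) as the outcome. Regress it on arm, pre-test score and arm × pre-test. The control group's post-rehabilitation test must not be used here, because by then both arms have been treated.
- Report the interaction slope with its CI, labelled exploratory.
- Describe any R-squared on the pre-test as prognostic only. State what the slope method is, and whether the outcome is change or post-test score.
- State as a limitation that the unequal pre-post intervals could produce some slope difference without a treatment effect.

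The cost is wording in the analysis plan; no extra data are needed, since the control group's untreated retest is already scheduled. The price is imprecision. At 30 to 40 per arm only a large slope difference is likely to be detected, so the answer may well be that differential response was not shown.
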